#### Secondary Outcome Variables

To adjust for any confounding effects of changes in the intake of Vitamins C, B2, B6, B12 or folate that might affect haematological status measurements were made of these nutrients. Plasma vitamin C was measured by a fluorometric assay using a COBAS Bio centrifugal analyser [8]. Plasma pyridoxal phosphate and pyridoxic acid, as measures of vitamin B6 status, were measured using an HPLC kit (Chromsystems, Munich, Germany). The routine clinical chemistry laboratory at the Royal Hallamshire Hospital measured plasma vitamin B12, and plasma folate was measured as 5-methyltetrahydrofolate by isocratic reverse phase HPLC [11].

Because of the documented influence that riboflavin status can have on plasma homocysteine concentration [12,13] plasma homocysteine was measured as an additional functional measure of riboflavin status using an iMX autoanalyser (Abbott Diagnostics, Maidenhead, Berks, UK).

In order to correct for increases in plasma ferritin as a result of underlying infection, plasma C-reactive protein was measured using an ELISA kit (Quantikine DCRP00 Human C-Reactive Protein Immunoassay, R&D Systems, Abingdon, UK).

### Data Analysis

For descriptive statistics baseline values will be analysed according to randomisation group. Data will be tested for normality using Shapiro-Wilk and Kolmogorov-Smirnov tests. Categorical variables will be tested using the Chi squared test and continuous variables compared across randomisation groups using ANOVA.

The effects of intervention on all continuous variables will be analysed by ANOVA. Where ANOVA indicates a significant difference across the randomisation groups a Scheffe test or Kruskal-Wallis Multiple Comparison Z-value test will be carried out, as appropriate, to identify where the differences lie.

Spearman Rank Correlations will be conducted to examine possible associations between selected continuous variables.

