### Randomisation to treatment

Randomisation was performed by an independent third party. Treatment codes were generated by ferritin stratification in blocks of 3 using a computer generated randomisation schedule. Three ranges of plasma ferritin were used for stratification; less than 15 ng/ml, 15.1–59.9 ng/ml and greater than 60 ng/ml. One in four women were allocated to the bioavailability arm by random sampling from those in the 4 mg and placebo groups of the intervention.

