### Intervention study clinics

#### Baseline Clinic (Week 0)

This was an opportunity to explain the study in more detail and answer any questions. The height and weight of each subject were measured. The completed food diary was returned by the volunteer and the responses discussed with the researcher. The next food diary was given and dates agreed for completion prior to the next visit. A fasted blood samples was taken (15 ml, EDTA vacutainer) for baseline biochemistry and haematological measurements. Volunteers were given capsules with instructions for their use.

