#### Post Intervention clinic (Week 8)

A fasted blood sample was collected (15 ml, EDTA vacutainer) for post intervention biochemistry and haematological measurements. Any remaining capsules were collected and counted.

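### The main-trial ANOVA names no baseline covariate, no ferritin-stratum term and no defined response; ANCOVA on the week-8 value would be more precise at almost no cost

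*Protocol article*

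**What the plan says.** The Data Analysis section of the protocol article gives one method for the main trial: "The effects of intervention on all continuous variables will be analysed by ANOVA". If the test across the three groups is significant, "a Scheffe test or Kruskal-Wallis Multiple Comparison Z-value test will be carried out, as appropriate, to identify where the differences lie". Its only stated use of baseline data is descriptive: "For descriptive statistics baseline values will be analysed according to randomisation group". The section names no covariate and no stratum term, and it does not say whether the analysed quantity is the week-8 value, the change from week 0 or a repeated measure.

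The design collects more than this model is said to use. Under Randomisation to treatment, "Treatment codes were generated by ferritin stratification in blocks of 3 using a computer generated randomisation schedule", and "Three ranges of plasma ferritin were used for stratification". Under Baseline Clinic (Week 0), fasted blood is drawn "for baseline biochemistry and haematological measurements", and under Post Intervention clinic (Week 8) it is drawn again "for post intervention biochemistry and haematological measurements".

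**The concern.** Each haematological outcome has a week-0 value, usually the strongest predictor of the same person's week-8 value. Randomisation was also balanced on ferritin, which is itself one of the primary outcomes. A model with neither term leaves explainable variation in the error.

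At stake is the chance of detecting the haemoglobin effect for which the trial was sized. On the article's own effect and SD, an analysis of week-8 values without covariates falls short of the 90% power claimed, and recruitment is over. The choice of model is the main place left to recover precision.

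The undefined response matters in its own right. A week-8 analysis and a change-score analysis can differ widely in precision, and the text lets either be chosen later.

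**Working it through.** **Inputs from the article.** Effect 0.7 g/dl; SD 1.05 g/dl, quoted with the baseline mean and so a between-person SD; 31 per arm for 90% power; target 40 per arm (Power Calculation, Details). Completers: 119 (Abstract, Discussion), and 119/3 = 39.7, so about 40 per arm.

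**Assumptions.** Two-sided 0.05 (the article gives 0.05 only for the bioavailability calculation, without sidedness); equal SD at weeks 0 and 8; and r, the baseline to week-8 correlation, which is not in the article and is shown over a range.

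**Step 1: the article's own figure.** For a two-group comparison, n per arm = 2 × [1.05 × (1.960 + 1.282)/0.7]² = 47.3, so 48 (49 by the t-test). The stated 31 is not reproduced. It would need a working SD of about 0.85, which corresponds to ANCOVA with r about 0.60 or change scores with r about 0.68. The article states neither. Whether 31 is right is a separate sample-size question; here it shows only that there is no spare power.

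**Step 2: residual SD under each analysis.**
- Week-8 value: 1.05.
- Change from baseline: 1.05 × √(2(1 − r)).
- ANCOVA on baseline: 1.05 × √(1 − r²).

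The variance ratios follow:
- ANCOVA to week-8 = 1 − r², below 1 for any non-zero r.
- ANCOVA to change = (1 − r²)/(2(1 − r)) = (1 + r)/2, below 1 for any r under 1.

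**Step 3: power for 0.7 g/dl at 40 per arm** (noncentral t, one pairwise contrast).

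| Assumed r | SD week-8 / change / ANCOVA | Power week-8 / change / ANCOVA |
|---|---|---|
| 0.3 | 1.05 / 1.24 / 1.00 | 84 / 70 / 87% |
| 0.5 | 1.05 / 1.05 / 0.91 | 84 / 84 / 93% |
| 0.7 | 1.05 / 0.81 / 0.75 | 84 / 97 / 98% |

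ANCOVA is highest in every row. Its margin over the week-8 analysis grows with r (3, 9 and 14 points), while its margin over change scores shrinks (17, 9 and about 2 points).

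**Step 4: the planned Scheffé step.** The table uses an ordinary t criterion. With Scheffé's criterion at 40 per arm, power for the same contrast is about 69% for the week-8 analysis, and 83%, 89% and 95% for ANCOVA at r = 0.5, 0.6 and 0.7.

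**Step 5: the strata.** Stratified blocks of 3 were simulated for 120 women, with assumed stratum shares of 30/60/10%. Where the stratum predicted the outcome, the type I error of the unadjusted week-8 ANOVA was 0.023 to 0.039 against a nominal 0.05; where it did not, 0.041 to 0.049. Once the baseline value was in the model, adding the stratum changed power by less than 1 percentage point.

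**The case against.** The strongest case on the other side has four parts.

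*The plan may use baseline after all.* A reader might infer that the analysis ignores baseline values. The article does not support that as fact, because the response is not defined. A change-score ANOVA uses the week-0 value, and so does a repeated-measures ANOVA. This stands. It does not remove the point, since ANCOVA is more precise than a change-score analysis for any r below 1, but at high r the loss is small: 97% against 98% power at r = 0.7.

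*The detail may sit in a fuller document.* The article is condensed, and covariates are often left to an analysis plan. The Secondary Outcome Variables section speaks of adjusting for vitamins and correcting ferritin for C-reactive protein, which the Data Analysis section does not repeat, so the latter may be a summary. This stands in part. Yet the section does not leave the method open: it names one for all continuous outcomes, while regression is named only for the bioavailability substudy.

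*The size rests on an assumed correlation, and the wrong sample size exaggerates it.* Both are correct. At r = 0.3 ANCOVA gains only 3 points over the week-8 analysis. At 31 per arm unadjusted power is 73%, but about 40 per arm completed, where it is 84%.

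*ANOVA across randomised arms is valid.* This stands. A reader might take the missing stratum term to mean biased estimates or excess false positives. Neither follows: leaving out a prognostic stratum makes the test conservative. Nor would the stratum term itself recover much power once baseline is adjusted for.

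**Conclusion.** The point holds as one of efficiency and of a poorly fixed method. The named ANOVA has no baseline covariate, no stratum term and no defined response, and on either plausible reading it is less precise than ANCOVA.

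The direction of the loss needs no particular r, only that r is not 0 (week-8 reading) or is below 1 (change reading). Its size cannot be fixed from the article. At about 40 per arm, ANCOVA gains between 3 and 14 points of power over the week-8 analysis for r from 0.3 to 0.7, and between 17 and about 2 points over change scores across the same range. These figures also rest on a two-sided 0.05 test, equal SDs at both visits and the article's SD of 1.05.

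The stated analysis is neither biased nor anti-conservative, and the article does not establish that baseline is ignored.

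**What to change.** In the Data Analysis section, name the week-8 value as the response for each continuous outcome. Analyse it by ANCOVA with treatment (three levels), the week-0 value of that outcome and the ferritin stratum as randomised. Use the log scale for skewed markers such as ferritin. The stratum term is there to reflect the design; little extra power should be expected from it.

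**Cost.** No new data are needed. The model spends 1 degree of freedom on baseline and 2 on the strata, so 3 of about 116 (119 completers less 3 group means). The real cost is timing: the Discussion says the trial is complete and the analysis underway. The model should therefore be written down and dated before treatment codes are revealed. If that moment has passed, the report should disclose when the choice was made.

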## Methods/Design

The study design was a randomised, double-blind, placebo-controlled, intervention trial in which participants received one of two daily doses of riboflavin or placebo over a period of eight weeks and effects on measures of iron status and iron handling were evaluated. Ethical approval for the study was granted by the Sheffield University Research Ethics Committee (SMBRER15).

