### Details

We calculated that to achieve a 0.7 g/dl improvement in Hb in a population with an estimated baseline Hb of 13.5 g/dl (SD 1.05) [2] we required 31 subjects per arm of the study. This would give a power of 90%. We aimed to recruit 40 volunteers to each arm, allowing close to 15% dropout.

Based on an expected level of deficiency in this population of 66% it was anticipated that we would need to screen at least 200 young women.

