### Bioavailability data analysis

Statistical analysis will be performed at IFR using R data analysis software [14]. Standard Linear Regression and ANOVA models will be used. For all models, regression diagnostics will be checked to determine if data transformations, outlier omissions or alternative non-parametric models are required. Results will be considered significant if P < 0.05 for all tests.

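### Scheffe protects more contrasts than this three-arm trial needs: about 69% power per dose at 40 per arm, against 73% with Tukey or 77% with Dunnett

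*Protocol article*

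**What the plan says.** The Methods/Design section describes a placebo-controlled trial in which "participants received one of two daily doses of riboflavin or placebo". The Data Analysis section tests the intervention effect on every continuous variable by ANOVA across the three groups, and then: "Where ANOVA indicates a significant difference across the randomisation groups a Scheffe test or Kruskal-Wallis Multiple Comparison Z-value test will be carried out". The stated purpose of that second step is to locate the differences. No particular contrast is named.

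The Details paragraph of the Power Calculation section sizes the trial on a single haemoglobin difference. The aim is "to achieve a 0.7 g/dl improvement in Hb", with an SD of 1.05 attached to the baseline value; "we required 31 subjects per arm of the study"; and "This would give a power of 90"%. The recruitment target follows: "We aimed to recruit 40 volunteers to each arm, allowing close to 15% dropout". The paragraph mentions no allowance for three arms or for a multiple-comparison procedure.

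**The concern.** The point does not depend on anything a separate analysis plan might add, because the Data Analysis section itself prescribes the follow-up test. Scheffe holds the familywise error over all linear contrasts among the three means. A trial of two doses against placebo needs two of these contrasts, or three if the doses are also compared with each other. Cover for contrasts that nobody intends to test is paid for with a larger critical value.

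At stake is the chance of showing that a given dose differs from placebo when it does. There is also a chance of an awkward result: a significant ANOVA with neither dose separated from placebo.

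A smaller point is that the rank-based follow-up is, as worded, also reached through a significant ANOVA. Read literally, an outcome that failed the planned normality checks would still have to pass a parametric F test first.

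**Working it through.** **Inputs.** Difference 0.7 g/dl, SD 1.05, 31 required and 40 targeted per arm (Power Calculation, Details). Three equal arms are inferred from the blocks of 3 under Randomisation to treatment. The haemoglobin calculation gives no significance level. The Bioavailability data analysis section says "Results will be considered significant if P < 0.05 for all tests", so two-sided 0.05 is assumed here. The Abstract reports 119 completers, or 119/3 = 39.7 per arm if balanced, so the 40-per-arm figures also describe the trial as run.

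**The plan's own figure first.** n per arm = 2 × 1.05² × (1.960 + 1.282)² / 0.7² = 47.3, so 48 per arm for 90% power (49 with the t distribution). The stated 31 is not reproduced. At 31 per arm the same formula gives 74.7% power. A sample size of 31 would fit an SD of about 0.85, which the article does not state.

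**Critical values for |t| at 40 per arm (117 df).**
- Scheffe: √(2 × F(0.95; 2, 117)) = 2.48
- Tukey (studentised range / √2): 2.37
- Dunnett, two contrasts (simulated): 2.24
- Unadjusted: 1.98

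**Power for one dose against placebo.** This is noncentral t with 3n − 3 df and noncentrality 0.7 / (1.05 × √(2/n)), which is 2.98 at n = 40 and 2.62 at n = 31.

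| Per arm | Scheffe | Tukey | Dunnett | Unadjusted |
|---|---|---|---|---|
| 40 | 69.2% | 72.8% | 77.1% | 84.1% |
| 31 | 55.6% | 59.7% | 64.8% | 73.8% |

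For 90% per dose, Scheffe needs 64 per arm, Dunnett about 57 and an unadjusted test about 48.

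**Error actually used.** With no effect anywhere and 40 per arm, 1,000,000 simulated trials give a 2.7% chance that Scheffe declares either dose different from placebo. Dunnett is constructed to use the full 5%.

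**Does the ANOVA gate add to the loss?** In 400,000 simulated trials per pattern of means, power for the Scheffe contrast was the same with and without the gate (69.2% in both cases when both doses work). A significant Scheffe contrast implies a significant F, so the gate costs nothing while Scheffe is used. It would cost something with Dunnett. If the true effects are 0.35 and 0.7, F is significant in 75.4% of trials, but ungated Dunnett shows the larger effect in 77.0%. Gating would therefore lose at least 77.0 − 75.4 = 1.6 points.

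**Significant ANOVA, neither dose separated from placebo (40 per arm).**
- Both doses at 0.7: 87.0% − 83.4% = 3.6%
- Effects 0.35 and 0.7: 75.4% − 70.5% = 4.9%
- Only one dose at 0.7: 87.0% − 69.7% = 17.3%

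**Sensitivity to the SD (40 per arm).**

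| SD | Scheffe | Dunnett | Unadjusted |
|---|---|---|---|
| 0.8 | 92.2% | 95.2% | 97.3% |
| 0.9 | 83.9% | 89.1% | 93.2% |
| 1.05 | 69.2% | 77.0% | 84.1% |
| 1.2 | 55.3% | 64.4% | 73.5% |

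This table fixes the Dunnett value at 2.24, hence 77.0% rather than 77.1%.

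**The case against.** The best defence is that the article never says it asks only two questions. Its aim of locating the differences covers all three pairs. On that reading the fair comparator is Tukey, and the loss is 72.8% − 69.2% = 3.6 points rather than about 8. This stands as a limit on the size, but Scheffe remains the less efficient choice on either reading. Scheffe would also cover a contrast of both doses pooled against placebo, with about 83% power at 40 per arm if both work. The plan names no such contrast.

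A reader might infer that an F gate followed by Scheffe corrects twice. It does not: the gate removes no Scheffe rejection, so dropping it while keeping Scheffe would recover nothing.

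A reader might also set 69% against the stated 90% and blame Scheffe for the whole gap. At 40 per arm an unadjusted test reaches only 84%, so that part belongs to the sample-size calculation and is a separate matter. Of the fall from 84% to 69%, Dunnett would itself cost about 7 points.

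On the rank-based branch, a condensed article may use ANOVA loosely for either the parametric or the rank version, and the section does let the follow-up test depend on the data. The wording permits the literal reading but does not prove it was intended, and no magnitude can be attached to it.

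**Conclusion.** The point holds as one of efficiency. On the plan's own difference and SD, with two-sided 0.05 assumed and equal arms, Scheffe gives about 69% power per dose at 40 per arm, some 4 points below Tukey and 8 below Dunnett. The whole of that loss comes from its critical value.

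The absolute figures rest on the baseline SD of 1.05. An analysis of change, or one adjusted for baseline, would have a different SD, and the penalty in points shrinks as power rises. It is about 3 points against Dunnett at SD 0.8 and 9 at SD 1.2. The figures apply to haemoglobin on the Scheffe branch only.

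The documents do not support a charge of invalidity, because the error rate across the three groups within one outcome is controlled. An ANOVA that is significant without separating either dose from placebo is uncommon (about 4%) if both doses work. It becomes frequent (about 17%) only if one of them has no effect. The change is worth making because Tukey or Dunnett raises power while still holding the familywise error for their contrasts at 5%.

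**What to change.** Name the contrasts, and replace Scheffe in one of two ways.

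- **Dunnett:** 2 mg against placebo and 4 mg against placebo, with simultaneous 95% confidence intervals, not conditional on the F test. The cost is that 2 mg against 4 mg becomes descriptive.
- **Tukey:** if all three pairs are wanted. This has no downside for pairwise comparisons.

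For outcomes that fail the normality checks, do not make the rank-based comparison conditional on a significant parametric ANOVA.

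The change needs wording and no new data, but timing matters. The Discussion says the trial is complete and the analysis has begun, and the new test is less strict than the one published. The chance of a false dose-versus-placebo claim per outcome rises from 2.7% to the nominal 5% with Dunnett. Make the change before unblinding; otherwise date it and report it as a deviation.

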### Screening Clinic

The purpose of the screening clinic was four fold: -

1. to establish eligibility on the basis of the inclusion and exclusion criteria

2. to provide the volunteer with further information and gain informed consent for the whole study including the bioavailability arm

3. to collect the following demographic and health information by personal interview: -

• date of birth

• contact details

• GP address

• the use of medication

• supplement use

• the presence of known food allergies

• the existence of any medical conditions

• smoking status

• menstrual information – date of last period, length of cycle and contraceptive usage

4. to collect a 500 μl, non-fasted, finger prick sample for the measurement of riboflavin status (EGRAC) and plasma ferritin concentration.

Women with an EGRAC >1.40 were considered to be moderately riboflavin deficient and were invited to take part in the intervention study. Those women accepting the invitation were randomised to receive one of three supplements; 4 mg riboflavin, 2 mg riboflavin or placebo. The capsules were formulated by Research Products Limited (RPL, Blackpool) and were suitable for vegetarians and vegans (gelatin-free and coloured with chlorophyll). The researchers and participants were blinded to the identity of each capsule; only the suppliers of the capsules and an independent third party responsible for the randomisation knew the identity. The capsules, packed in pots of 60, were given at the first baseline visit and were sufficient for the entire intervention allowing 4 spare capsules for any losses. The riboflavin content in a random sample of each type of capsule was checked by high performance liquid chromatography.

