### Outcome Variables

#### Primary Outcome Variables

To assess haematological parameters the following were measured in the haematology laboratory at the Royal Hallamshire Hospital, Sheffield: red blood cell count, PCV, MCV, MCHC, haemoglobin and ZPP. ELISA kits were used to measure plasma ferritin (Spectro Ferritin Kit, ATi Atlas Ltd. Chichester, UK) and plasma soluble transferrin receptor (Quantikine DTFR1 – Human sTfR Immunoassay, R&D Systems, Abingdon, UK)

Riboflavin status was measured by the EGRAC assay [5] and plasma flavin concentration measured using an HPLC kit method (Chromsystems, Munich, Germany).

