#### Influence of recruitment to screening on riboflavin status

It was considered possible that the time taken between screening and starting the intervention trial might influence dietary change prior to starting the intervention. The median time that women had to wait before starting the intervention was 47 days (range 7–240). The main reason for delay was the coordination of the start of the study with the menstrual cycle. Other factors included the timing of vacations and the need to accommodate 4–6 visits over a period of 12–14 weeks depending on the arm of the study.

The mean EGRAC value for the entire screened population (n = 256) was 1.43 ± 0.18.

This is comparable with the EGRAC values reported in the most recent Diet and Nutrition Survey of adults in the UK for this age group (mean, 1.45 ± 0.19).

The mean (± SD) EGRAC value of these women recruited to the intervention study was 1.54 ± 0.14. The mean EGRAC value at baseline was significantly greater (1.59 ± 0.19) indicating a modest but significant deterioration in riboflavin status during the waiting period (*P *= 0.007)

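### EGRAC and plasma flavin are committed to a common-variance ANOVA and Scheffe analysis although riboflavin may change their spread by arm, so the 2 mg versus 4 mg comparison may use the wrong standard error

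*Protocol article*

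**What the plan says.** The Data Analysis section of the protocol article fixes one method for the main study: "The effects of intervention on all continuous variables will be analysed by ANOVA". If the ANOVA is significant, "a Scheffe test or Kruskal-Wallis Multiple Comparison Z-value test will be carried out, as appropriate, to identify where the differences lie". The only assumption check named there is of distributional shape: "Data will be tested for normality using Shapiro-Wilk and Kolmogorov-Smirnov tests". Nothing is said about equal variances. The Bioavailability data analysis section, by contrast, provides for regression diagnostics and for transformations or alternative models where needed.

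The Screening Clinic section has women "randomised to receive one of three supplements; 4 mg riboflavin, 2 mg riboflavin or placebo". Under Primary Outcome Variables, next to the haematological measures, stands: "Riboflavin status was measured by the EGRAC assay [5] and plasma flavin concentration measured using an HPLC kit method".

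The article gives EGRAC spread only before treatment and not by arm. At screening, the "EGRAC value of these women recruited to the intervention study was 1.54 ± 0.14". At the start of the intervention, "The mean EGRAC value at baseline was significantly greater (1.59 ± 0.19" for SD).

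**The concern.** ANOVA and its Scheffe follow-up estimate one residual variance from all three arms. The placebo arm's scatter therefore enters the standard error for 2 mg against 4 mg, although no placebo woman takes part in that contrast. This is harmless if the arms are equally variable.

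EGRAC and plasma flavin are the two primary variables where equal spread is least safe to assume, because the supplement acts on them directly. EGRAC reflects how far glutathione reductase lacks its cofactor. Women selected for deficiency and then supplemented may converge, while placebo women stay scattered. Plasma flavin may do the opposite and spread out with dose. Normality tests are not designed to detect either pattern.

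At stake is whether 4 mg raises riboflavin status beyond 2 mg. If EGRAC narrows on treatment, a non-significant result could be read as no added effect of the higher dose when placebo scatter hid the difference. If plasma flavin widens, the same test rejects too readily relative to a test with the correct variance.

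**Working it through.** **The plan's own figure.** None exists for this comparison. The sample size in the Details section concerns haemoglobin, so there is no stated power to reproduce.

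**Inputs from the article.** Three arms; 40 per arm ("We aimed to recruit 40 volunteers to each arm, allowing close to 15% dropout"); baseline EGRAC SD 0.19, used here as the placebo SD at week 8.

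**Assumptions.** Both riboflavin arms have SD s, from 0.06 to 0.19. The true 2 mg to 4 mg difference is 0.63s, which an uncorrected two-arm unequal-variance test detects with about 80% power. Placebo lies far enough away that the overall ANOVA is significant. Data are normal, week-8 values are analysed, and alpha is 0.05 two-sided.

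**Step 1: inflation from pooling.** Pooled SD = sqrt((0.19² + 2s²)/3), and k = pooled SD / s.

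**Step 2: power for 2 mg versus 4 mg.** The Scheffe cutoff is |t| > sqrt(2 × F(0.95; 2, 117)) = 2.48, with 117 = 3 × 39. In units of the pair's own standard error, s × sqrt(2/40), the true difference is 0.63 × sqrt(20) = 2.82. Approximate Scheffe power is therefore P(Z > 2.48k − 2.82). Games-Howell uses the pair's own variance and a cutoff of about 2.39, which gives P(Z > 2.39 − 2.82) = 67% whatever s is.

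| Active SD s | Pooled SD | k | Scheffe, formula | Scheffe, simulated | Games-Howell, simulated |
|---|---|---|---|---|---|
| 0.19 | 0.190 | 1.00 | 63% | 63% | about 67% |
| 0.14 | 0.158 | 1.13 | 50% | 51% | about 67% |
| 0.12 | 0.147 | 1.23 | 41% | 42% | about 67% |
| 0.08 | 0.128 | 1.60 | 13% | 14% | about 67% |
| 0.06 | 0.120 | 2.00 | 2% | 3% | about 67% |

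The simulation applies Scheffe after a significant ANOVA. The first row isolates Scheffe's own conservatism (63% versus 67%). The further fall down the table comes from pooling.

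**Step 3: spread that rises with dose (plasma flavin).** No SD is given for this variable, so take SD ratios 1:2:3 for placebo, 2 mg and 4 mg. The pooled variance is (1 + 4 + 9)/3 = 4.67, and the pair's own is (4 + 9)/2 = 6.5, a ratio of 0.72. The Scheffe cutoff in the pair's own units falls to 2.48 × sqrt(0.72) = 2.10. The simulated false-positive rate for 2 mg versus 4 mg is about 4%, against about 2% with Games-Howell.

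**Step 4: change from baseline.** The section does not say whether week-8 values or changes are compared. With baseline SD 0.19 and an assumed correlation of 0.7 on placebo, the placebo change SD is sqrt(2 × 0.19² × 0.3) = 0.147. With treated week-8 SD 0.08 and correlation 0 to 0.5, the treated change SD is sqrt(0.19² + 0.08²) = 0.206 down to sqrt(0.19² + 0.08² − 0.19 × 0.08) = 0.165. Placebo is then the less variable arm, and the EGRAC direction reverses.

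**Step 5: dose versus placebo.** Under the planned ANOVA and Scheffe, the per-comparison error at active SD 0.06, 0.08 and 0.12 is about 4%, 3% and 2%, below 5% in each case.

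**The case against.** The strongest reply is that the driving figure is not in the document. The article does not say that riboflavin will change the spread of either variable, and it gives no post-treatment or by-arm SD. That stands: the EGRAC loss runs from nothing beyond Scheffe's conservatism to nearly all the power, and Steps 3 and 4 show that the direction can turn. A reader might infer that the dose comparison is bound to lose most of its power on both variables. The document does not support that.

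A reader might also infer that pooling raises the dose-placebo error to 7–10%. Those figures belong to an uncorrected pooled t test, which is not planned. Under Scheffe the rate is about 2–4%.

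Nor is any power claim contradicted. The trial was sized on haemoglobin, and no objective names 2 mg versus 4 mg on EGRAC.

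Two further replies carry less weight. First, the section allows a rank-based test, which does not pool the raw variance. But its ranks still span all three arms. At a difference of 0.74 active SDs, with active SD 0.07 to 0.19, its simulated power was 39–56% with a Bonferroni cutoff and 65–77% with a 1.96 cutoff. The Scheffe cutoff with the pair's own variance gave 78–79%. Second, variance checks are often left to an analysis plan that is not shown. Silence alone would indeed be no finding, but this section commits every continuous variable to a named common-variance method.

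**Conclusion.** The point holds as a modest improvement, not as an error that undermines the trial. The plan commits two primary variables whose spread may well depend on treatment to a method that assumes it does not, and it names no check of that assumption. If week-8 EGRAC narrows to an active SD between 0.06 and 0.14, Scheffe power for 2 mg versus 4 mg is about 3% to 51%, where Games-Howell gives about 67%. At equal SDs the gap is only 63% versus 67%. If plasma flavin widens as 1:2:3, the comparison is more liberal instead. These figures rest on 40 per arm, normal data, the assumed SDs and a difference of 0.63 active SDs. The haemoglobin sample size is unaffected.

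**What to change.** Add one sentence to the Data Analysis section: EGRAC and plasma flavin will be compared by Welch ANOVA with Games-Howell pairwise comparisons, or by a linear model with a separate residual variance for each arm. Fix this before unblinding and do not let a preliminary variance test choose the method. The article reports that the analysis is already underway; if it has been unblinded, report the unequal-variance analysis as a declared sensitivity analysis.

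The cost is a negligible loss of degrees of freedom if the variances turn out equal. Even then, Games-Howell loses nothing against Scheffe for this comparison (about 67% versus 63%). In return, the standard errors are valid whichever arm is more variable, so the unknown direction does not matter.
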